#### Study centers

The study will be conducted on a national multicenter basis. The coordinating center is the Division of Clinical Epidemiology of Early Cancer Detection, German Cancer Research Center, Heidelberg. Recruitment is planned to be conducted within 2–3 years in 10 German hospitals in the following towns: Cologne, Heidelberg, Berlin, Essen, Augsburg, Tübingen, Gießen, Stuttgart, Erlangen, and Frankfurt am Main (see Supplemental Material for the institution’s names). The coordinating center will create packages with all study materials and trial drugs needed for a study participant, which are all labelled with the randomization ID (RandomID), which will be supplied by the Pharmacy of the University Clinic Heidelberg, which has the randomization list. The study centers will assign these RandomIDs consecutively to the patients in the timely order of study inclusion and document the RandomID together with the study participants’ name and date of birth in the eCRF.

### Study population

Inclusion and exclusion criteria are listed in Table 1.

**Table 1 Tab1:** Inclusion and exclusion criteria

Inclusion Criteria	Exclusion Criteria
– Age ≥ 18 years – Diagnosis of CRC (ICD-10: C18-C20; any stage) – Planned CRC resection in one of the up to 12 cooperating German hospitals within the next 14 days – Willingness to complete the pre-surgery questionnaire and to provide the first blood and stool sample or rectal swab before the surgery – Informed consent to participate in the LEONORA trial	– Patient with any social or logistical condition, which in the opinion of the investigator may interfere with the conduct of the study, such as incapacity to understand well, not willing to collaborate, or cannot easily be contacted after discharge – Previous participation in this study – Parallel participation in another interventional trial with a nutritional intervention – Pregnant women – Use of immunosuppressants (Systemic glucocorticoids with a daily dosage of more than 10 mg prednisolone (or equivalent) or drugs of ATC group L04A, except neoadjuvant or adjuvant chemotherapy or radiotherapy for CRC treatment). – Insulin-dependent diabetes – Withdrawn consent prior use of trial medication

*Abbreviations:*
*CRC* colorectal cancer, *ICD* International Classification of Diseases, *ATC* Anatomical Therapeutical Chemical classification

### Study endpoints

The primary endpoint of the study is the gastrointestinal function-related quality of life 90 days after surgery, as assessed by the Gastrointestinal Quality of Life Index (GIQLI) total score [26].

Secondary endpoints ascertained during interventional study phase.

GIQLI total score 30 days after surgery.GIQLI subscales 30 and 90 days after surgery: symptoms (e.g. diarrhea, flatulence and constipation), physical functions, emotions and social function subscale.Changes in GIQLI total score and sub-scales from pre-surgical visit to day 30 and 90.Low Anterior Resection Syndrome (LARS) Score at day 90 after surgery.Further quality of life total and sub-scales (EQ-5D-5 L, EORTC QLQ-C30, and EORTC QLQ-CR29) 30 and 90 days after surgery and their changes from pre-surgical visit to day 30 and 90.Fatigue scale (EORTC-FA12) and sub-scales at day 90 after surgery.Anxiety (GAD-7) at day 90 after surgery.Cost-effectiveness (costs per prevented diarrhea case) and cost-utility of the intervention (costs per quality adjusted life-year (QALY) gained, as assessed with the EQ-5D-5 L).Emergence of multidrug-resistant organisms (MDRO) until day 90.Rate of physician-documented infections (bloodstream infection (BSI), catheter-related BSI, pneumonia, surgical site infections, intra-abdominal infections, and urinary-tract infections) until day 30 and day 90.Rate of self-reported infections (upper and lower respiratory tract infections, gastro-intestinal tract infections, bladder infections, wound infections, other infections and episodes with high fever (≥ 38 °C)) until day 30 and day 90.Total rate of infection until day 30 and day 90.Antibiotics use (Yes/No and number of days) until day 30 and day 90.Rates of post-operative complications, defined as the following 4 clinical events: Initiation of antibiotic or antifungal treatment, surgical revision, new mechanical ventilation, sepsis or death until day 90.Time from CRC surgery to hospital discharge.Number and length of re-hospitalizations until day 90.Changes in the gut microbiome composition until day 30 and day 90.Concentration changes of biomarkers of inflammation and immune function in serum samples collected prior surgery and 90 days after surgery (89 proteins of the combination of the OLINK^®^ Target 48 Cytokine panel and the OLINK^®^ Target 48 Immune Surveillance panel, including, for example, interleukin-6 as well as biomarkers of systemic inflammatory response (C-reactive protein (CRP), mGPS (modified Glasgow prognostic score), HS_mGPS (high-sensitive mGPS), NLR (neutrophil-to-lymphocyte ratio), PLR (platelet-to-lymphocyte ratio), LMR (lymphocyte-to-monocyte ratio), SII (systemic immune-inflammation index), PNI (prognostic nutritional index), and NPS (neutrophil-platelet score))).Concentration changes of metabolomic biomarkers (pre-defined selection of amino acids, fatty acids, and bile acids measured with high accuracy with targeted LC-MS/MS and the total metabolome measured with untargeted LC-MS/MS, which has lower accuracy) in fecal and plasma samples collected prior surgery and 90 days after surgery.

Secondary endpoints with long-term, observational follow-up data.

Quality of life total and sub-scales (GIQLI, EQ-5D-5 L, EORTC QLQ-C30, and EORTC QLQ-CR29) 6, 12, and 24 months after surgery and their changes from pre-surgical visit to day month 6, 12, and 24.Fatigue (EORTC-FA12 and its subscales) at month 6, 12, and 24.Depression (CESD-R and its subscales) at month 6, 12, and 24.Rate of self-reported infections (upper and lower respiratory tract infections, gastro-intestinal tract infections, bladder infections, wound infections, other infections and episodes with high fever (≥ 38 °C) until month 6, 12, and 24.Antibiotics use (Yes/No and number of days) until month 6, 12, and 24.Changes in the gut microbiome composition until month 6 and 12.Number and length of re-hospitalizations until month 6, 12, and 24.2-5-year overall survival, disease-free survival, and progression-free survival rate.

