### Aims of the study

The main objective of this study is to test whether the early post-surgical administration of synbiotics has an impact on the gastrointestinal function-related quality of life 90 days after surgery. Further objectives are to test the efficacy of the intervention on rates of infection, inflammatory biomarkers, and recurrence-free survival. Stool samples will be collected to additionally address changes in microbiota composition.

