### Study visits

Table 2 gives an overview on the study visits and more details follow in text below the table.

**Table 2 Tab2:** Study visits of the LEONORA study

Study visit	Time point	Intervention(s) / Procedure(s)
Pre-surgery visit	Day − 13 prior surgery to day of surgery	Informed consent, randomization, 1st questionnaire, 1st fecal sample (or rectal swab) and 1st blood sample.
Post-surgery visit	Day 1–3 post surgery	Handing out of trial medication and patient diary. Start of treatment as soon as liquid diet is being tolerated for 12 weeks (84 days).
Continuous monitoring for appearance of clinical events and compliance	Day 1 – Hospital discharge	Screening for clinical events (antibiotic/antifungal treatment, surgical revision, ventilation, sepsis or death), and monitoring of regular intake of study medication daily until hospital discharge. If a clinical event is detected, information will be documented in the eCRF.
Day 30 visit	Day 28–49 post surgery	2nd questionnaire and 2nd fecal sample.
Day 90 visit	Day 87–108 post surgery	End of trial. 3rd questionnaire, 3rd fecal sample, 2nd blood sample, and collection of filled patient diary.
Month 6 follow-up visit	Day 183–218 post surgery	4th questionnaire and 4th fecal sample. Collection of data on hospitalizations, infections, cancer treatments, cancer incidence/re-occurrence and vital status at authorities and/or general practitioners/oncologists.
Year 1 follow-up visit	Day 365–400 post surgery	5th questionnaire and 5th fecal sample. Collection of data on hospitalizations, infections, cancer treatments, cancer incidence/re-occurrence and vital status at authorities and/or general practitioners/oncologists.
Year 2 follow-up visit	Day 730–765 surgery	6th questionnaire. Collection of data on hospitalizations, infections, cancer treatments, cancer incidence/re-occurrence and vital status at authorities and/or general practitioners/oncologists.

*Abbreviations:*
*eCRF* electronic Case Report Form

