#### Month 6 (Day 183–218), year 1 (Day 365–400), and year 2 (Day 730–765) follow-up visits

At these times, staff of the coordinating center will send the study participants the 4th, 5th, and 6th questionnaires. Furthermore, the 4th and 5th fecal sample collection will take place at the month 6 and year 1 visit in the same way as in the visits before.

Furthermore, the coordinating center will contact study participants’ general practitioners and/or oncologists in order to obtain medical records about cancer treatments and infections after release from the hospital and the course of the treatment (incl. re-hospitalizations and cancer recurrence). At the same time, if the staff of the coordinating center was unable to contact a study participant by telephone or mail, the authorities (residents’ registration office, registry office, and/or health authority) will be contacted to find out about the current address and vital status (cause of death, if applicable). If establishing a phone contact with a study participant is difficult, filling out the questionnaires can take place up to 6 months after the planned date.

As the availability of information at authorities about the vital status and cause of death can be delayed by up to 2 years, and the recruitment time will be 2–3 years, we will store the personal data needed for these inquiries for a minimum of 6 years. The obtained overall, cancer, and CRC-specific survival time will vary from 2 to 5 years for the study participants because the mortality follow-up will end at a fixed date (31 Dec 2030). This implies that the last recruited study participant will have the shortest observation period of approx. 2 years, and the first recruited study participant will have the longest observation period of approx. 5 years.

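### Disease-free and progression-free survival are listed as 2-5-year rates, but recurrence is last collected at year 2, so rates beyond about 2 years cannot be obtained from the planned data

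*Protocol article*

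**What the plan says.** The Study endpoints section closes its list of long-term observational endpoints with one entry, prefixed 2-5-year, for "overall survival, disease-free survival, and progression-free survival rate".

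Table 2 under Study visits has as its last row "Year 2 follow-up visit Day 730–765 surgery". That row provides for "6th questionnaire. Collection of data on hospitalizations, infections, cancer treatments, cancer incidence/re-occurrence and vital status". The same kind of collection is scheduled at month 6 and year 1, and no row follows year 2. The Questionnaire data section adds recurrence questions to every follow-up questionnaire from day 90 on, so the first inquiry is at day 90 and the last is still at year 2.

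The text on the month 6, year 1 and year 2 visits describes the request to general practitioners and oncologists for records on "the course of the treatment (incl. re-hospitalizations and cancer recurrence", at those same three contacts. It allows a questionnaire to be completed up to six months late when telephone contact is difficult. What continues afterwards is named separately: "the mortality follow-up will end at a fixed date (31 Dec 2030". The 2-to-5-year range given there is for overall, cancer and CRC-specific survival time. DFS and PFS are not mentioned. The retention of personal data for at least six years is tied to inquiries about vital status and cause of death.

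**The concern.** DFS and PFS need two kinds of event: death, and recurrence or progression. The endpoint list gives them the same horizon as overall survival, but after year 2 the schedule supplies only the first kind. A patient who relapses in year 3 and is alive at the end of 2030 leaves no trace of the relapse in the planned data.

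At stake is whether a listed endpoint can be delivered on its stated horizon. The article gives a full visit table, a horizon for the endpoint and a description of what continues after year 2, and these three do not fit together. An analysis plan that is not shown could settle definitions and censoring, but it cannot supply recurrence data that nobody collects.

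**Working it through.** **Inputs from the protocol**
- First inclusion: September 2025 (Trial status).
- Recruitment: 2 to 3 years (Study centers), so last inclusion is about September 2027 or September 2028.
- Mortality cut-off: 31 December 2030 (follow-up visits).
- Last recurrence inquiry: day 730 to 765 (Table 2). The midpoint is 747.5 / 365.25 = 2.05 years.
- Permitted questionnaire delay: up to 6 months, so about 2.5 years at the latest.

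**Step 1: reproduce the stated 2-to-5-year observation**
- First patient: September 2025 to the end of 2030 = 5.3 years.
- Last patient: 3.3 years with 2-year recruitment, 2.3 years with 3-year recruitment.

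The protocol's approximate range of 2 to 5 years is reproduced for mortality. For recurrence it is not: that stops at about 2.05 years for everyone (2.1 years at day 765).

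**Step 2: length of the gap, counted from day 765**
- First patient: about 3.2 years.
- Last patient: about 0.2 years (3-year recruitment) to 1.2 years (2-year recruitment).

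**Step 3: share of potential follow-up without recurrence ascertainment**

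Assumptions: even recruitment, deaths ignored. Share = 1 − covered time / mean follow-up.

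| Recruitment | Mean follow-up | Covered 2.05 years | Covered 2.5 years |
|---|---|---|---|
| 3 years | (5.3 + 2.3) / 2 = 3.8 | 1 − 2.05/3.8 = 46% | 1 − 2.5/3.8 = 34% |
| 2 years | (5.3 + 3.3) / 2 = 4.3 | 1 − 2.05/4.3 = 52% | 1 − 2.5/4.3 = 42% |

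The last column supposes that every year 2 contact used the full delay. These are shares of potential time, not the bias of any estimate.

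**Step 4: the two ways to analyse the data**
- *Censor at the last recurrence inquiry.* No patient is at risk after about 2 to 2.5 years, so no 3-, 4- or 5-year DFS or PFS rate exists. There is no overestimation.
- *Run time to the mortality cut-off.* Only deaths count after year 2, so surviving patients with a later recurrence are counted as event-free and the rate is too high.

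**Step 5: possible size on the second route (illustration only)**

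None of these inputs is in the protocol. Assume 2-year DFS of 70-80%, a recurrence hazard r of 0.02 to 0.06 per year after year 2, a death hazard d of 0.02 without recurrence and m of 0.30 after it. The overstatement of 5-year DFS is the proportion relapsed and alive three years later:

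DFS(2) × r / (m − r − d) × [exp(−3(r + d)) − exp(−3m)]

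- Low end: 0.70 × 0.02/0.26 × (0.887 − 0.407) = 2.6 percentage points (true 62.1%, apparent 64.7%).
- High end: 0.80 × 0.06/0.22 × (0.787 − 0.407) = 8.3 percentage points (true 62.9%, apparent 71.2%).

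**The case against.** **The horizon could be read differently.** The 2-5-year prefix might belong to overall survival alone, and the follow-up text does explain that range only for overall, cancer and CRC-specific survival. This is possible, but the entry as worded puts all three endpoints behind one prefix. On the other reading DFS and PFS would have no horizon at all. Either way the entry needs rewording.

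**Bias is not established.** A reader might infer that later recurrences will be counted as disease-free time and that the curves turn into mortality curves after year 2. The documents do not support that as a fact. The article gives no event definition or censoring rule for DFS and PFS, and such rules are commonly left to the analysis plan. The planned Cox model can accommodate censoring at the last recurrence inquiry. This objection stands against a claim of bias, but not against the finding that rates beyond about 2 years are unobtainable. Cause of death would reveal some late recurrences, but only in patients who die.

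**The recurrence aim can still be met.** The Aims section includes "rates of infection, inflammatory biomarkers, and recurrence-free survival". A reader might infer that this aim cannot be answered. It carries no horizon, however, and the scheduled inquiries can answer it at 2 years.

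**Naming and population are not defects here.** The variation between recurrence-free and disease-free survival, and the eligibility of any stage including stage IV, might also look like errors. They are matters of definition that an article commonly leaves to the full protocol or analysis plan.

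**The stakes are limited.** The endpoints belong to long-term observational follow-up, everything except the primary endpoint is declared exploratory, and both blinded arms follow the same schedule. All of this stands and limits the weight of the point.

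**Conclusion.** The point holds as a mismatch between endpoint and data collection. DFS and PFS are listed on a 2-5-year horizon, recurrence is last ascertained at about 2 years (about 2.5 with the permitted delay), and no section describes a later inquiry. The 2-year rate can be delivered; rates beyond that cannot, whichever censoring rule is used.

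The 46-52% of potential follow-up time without recurrence ascertainment (34-42% with the full delay throughout) rests on even recruitment and ignores deaths. The 2.6 to 8.3 percentage points rest on assumed hazards and apply only if time runs to the mortality cut-off. The point should be corrected, but it does not touch the primary analysis, the sample size or the 90-day endpoints.

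**What to change.** Choose one of two changes:

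1. In the endpoint list, keep the 2-5-year label for overall survival (and cancer and CRC-specific survival). State DFS and PFS as 2-year endpoints, censored at the date of the last recurrence inquiry. The cost is wording in the endpoint list and analysis plan, and a shorter stated horizon.
2. Keep the 2-5-year horizon and add a question to treating physicians on recurrence or progression, with its date, alongside the vital-status inquiry at the end of 2030. Add it to Table 2 and to the follow-up text. The cost is one further physician contact per surviving patient, and a check that consent and the retained personal data, now tied to vital-status inquiries, also cover it.

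The first patient was included in September 2025, so none reaches year 2 before September 2027. Either change can be made before then without losing data.

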### Study visits

Table 2 gives an overview on the study visits and more details follow in text below the table.

**Table 2 Tab2:** Study visits of the LEONORA study

Study visit	Time point	Intervention(s) / Procedure(s)
Pre-surgery visit	Day − 13 prior surgery to day of surgery	Informed consent, randomization, 1st questionnaire, 1st fecal sample (or rectal swab) and 1st blood sample.
Post-surgery visit	Day 1–3 post surgery	Handing out of trial medication and patient diary. Start of treatment as soon as liquid diet is being tolerated for 12 weeks (84 days).
Continuous monitoring for appearance of clinical events and compliance	Day 1 – Hospital discharge	Screening for clinical events (antibiotic/antifungal treatment, surgical revision, ventilation, sepsis or death), and monitoring of regular intake of study medication daily until hospital discharge. If a clinical event is detected, information will be documented in the eCRF.
Day 30 visit	Day 28–49 post surgery	2nd questionnaire and 2nd fecal sample.
Day 90 visit	Day 87–108 post surgery	End of trial. 3rd questionnaire, 3rd fecal sample, 2nd blood sample, and collection of filled patient diary.
Month 6 follow-up visit	Day 183–218 post surgery	4th questionnaire and 4th fecal sample. Collection of data on hospitalizations, infections, cancer treatments, cancer incidence/re-occurrence and vital status at authorities and/or general practitioners/oncologists.
Year 1 follow-up visit	Day 365–400 post surgery	5th questionnaire and 5th fecal sample. Collection of data on hospitalizations, infections, cancer treatments, cancer incidence/re-occurrence and vital status at authorities and/or general practitioners/oncologists.
Year 2 follow-up visit	Day 730–765 surgery	6th questionnaire. Collection of data on hospitalizations, infections, cancer treatments, cancer incidence/re-occurrence and vital status at authorities and/or general practitioners/oncologists.

*Abbreviations:*
*eCRF* electronic Case Report Form

#### Screening

Screening for eligible study participants will be done by a study nurse or study physician in the patient’s files (which captures clinical diagnoses) before or shortly after their admission to the hospital with a standardized screening checklist stating the in-and exclusion criteria.

#### Pre-surgery visit for information about the study (Day − 13 prior surgery to day of surgery)

During a first appointment in the hospital, eligible patients will be informed about the LEONORA study and the secondary data use in the National Center for Tumor Diseases (NCT) network by a study physician and will receive the printed study information documents. Written informed consent to participate in the LEONORA study will be obtained.

A study nurse or study physician will pick the baseline questionnaire from a study package, which is labelled with the RandomID, and give it to the study participant who shall fill it on the same day while being in the clinic. It is important that the study nurse takes a package with a RandomID starting with the letter “K” for a colon cancer patient or with a RandomID starting with the letter “R” for a rectum cancer patient. If a patient has both colon and rectum cancer, a package with a RandomID starting with a “K” shall be picked.

The study nurse or study physician will collect the baseline questionnaire, check it for completeness and will ask the study participant to complete the missing items immediately. The questionnaire will collect important data on the baseline levels of the quality of life endpoint scales and information needed to be able to contact the study participants for the follow-ups (name, sex, birthday, address and phone number).

Furthermore, the first stool sample will be collected on the Day − 13 to Day − 1 prior, with swabs that are labelled with the RandomID. If study participants cannot donate a stool sample in the given time frame, they will be asked to collect a rectal swab. The fecal sample should be obtained prior to the initiation of laxative treatment if performed pre-operative as part of routine patient management standards. Furthermore, 27 ml blood will be taken from each patient on the same day using tubes labelled with the RandomID. If possible, the blood sampling will be included in a regular blood sampling that is needed anyway for the routine patient care.

#### Post-surgery visit (Day 1–3 post surgery)

As soon as liquid diet is being tolerated (1–3 days after surgery), the trial nurse/physician will hand out the trial medication and the patient diary and explain their use to the patient. Both are labelled with the trial participants randomization ID. The day of the surgery is day 0 of the trial. The interventional phase starts with intake of the trial medication, which will last 12 weeks (84 days). The study participants are being asked to document intake of the trial drugs as well as all symptoms, new diagnosed diseases and injuries, which occurred during these 84 days, in the diary.

Continuous monitoring for appearance of clinical events and compliance (Day 1 – hospital discharge).

• Check for compliance and occurrence of a clinical event daily after surgery and until discharge. A clinical event refers to the occurrence of one of the 4 clinical incidents defined below.◦ Treatment: Initiation of antibiotic or antifungal treatment excluding perioperative or other prophylaxis.◦ Revision: Surgical revision or deep puncture / biopsy and/or interventional drainage (during endoscopic or percutaneous procedures) for any cause and any other consecutive abdominal surgery including repositioning of stoma.◦ Sepsis◦ Ventilation: New intubation and mechanical ventilation for any reason OR prolonged ventilation (≥ 24 h following surgery).

For each patient a maximum of three distinct clinical events is assessed. The first clinical event is triggered by the appearance of at least one of the above defined clinical incidents and may include further clinical incidents within 72 h (e.g. initiation of antibiotic treatment and intubation).If a clinical event occurs, it will be documented in detail in the eCRF.Readmission and occurrence of clinical events after the initial inpatient stay will be assessed by the patient diary, which will be filled until the Day 90 visit, and the Day 90 questionnaire. Medical records of patients with clinical events, including discharge letters, will be retrieved from the patients’ treating physicians by the coordinating center if deemed necessary for complete documentation.

